# The Prognosis in Palliative care Study II (PiPS2): study protocol for a multi-centre, prospective, observational, cohort study

**DOI:** 10.1186/s12904-018-0352-y

**Published:** 2018-08-13

**Keywords:** Cancer, Palliative care, Prognosis, Observational study

## Abstract

**Background:**

More accurate methods of prognostication are likely to lead to improvements in the quality of care of patients approaching the ends of their lives. The Prognosis in Palliative care Scales (PiPS) are prognostic models of survival. The scores are calculated using simple clinical data and observations. There are two separate PiPS models; PiPS-A for patients without blood test results and PiPS-B for patients with blood test results. Both models predict whether a patient is likely to live for “days”, “weeks” or “months” and have been shown to perform as well as clinicians’ estimates of survival. PiPS-B has also been found to be significantly better than doctors’ estimates of survival. We report here a protocol for the validation of PiPS and for the evaluation of the accuracy of other prognostic tools in a new, larger cohort of patients with advanced cancer.

**Methods:**

This is a national, multi-centre, prospective, observational cohort study, aiming to recruit 1778 patients via palliative care services across England and Wales. Eligible patients have advanced, incurable cancer and have recently been referred to palliative care services. Patients with or without capacity are included in the study.

The primary outcome is the accuracy of PiPS predictions and the difference in accuracy between these predictions and the clinicians’ estimates of survival; with PiPS-B being the main model of interest. The secondary outcomes include the accuracy of predictions by the Palliative Prognostic Index (PPI), Palliative Performance Scale (PPS), Palliative Prognostic score (PaP) and the Feliu Prognostic Nomogram (FPN) compared with actual patient survival and clinicians’ estimates of survival.

A nested qualitative sub-study using face-to-face interviews with patients, carers and clinicians is also being undertaken to assess the acceptability of the prognostic models and to identify barriers and facilitators to clinical use.

**Discussion:**

The study closed to recruitment at the end of April 2018 having exceeded the required sample size of 1778 patients. The qualitative sub-study is nearing completion. This demonstrates the feasibility of recruiting large numbers of participants to a prospective palliative care study.

**Trial registration:**

ISRCTN13688211 (registration date: 28/06/2016).

## Background

Patients approaching the ends of their lives, their relatives and clinicians all value accurate prognostic information [1–5]. This information is routinely provided by clinicians using their clinical intuition. However, clinicians’ estimates of survival (CES) are often inaccurate and over-optimistic [6]. The need for more accurate methods of prognostication was highlighted by the Neuberger report [7] into the short-comings of the implementation of the Liverpool Care Pathway [8].

Determining more accurately how long patients with advanced cancer have left to live would enable both patients and their relatives to make plans for their future [3]. It would also aid clinicians to target treatments to those patients most likely to benefit and it would safeguard other patients from receiving treatments that they are unlikely to benefit from [9]. Prognostic information may help clinicians to plan services and to ensure that patients are cared for in the most appropriate environment. More reliable prognostic estimates may also facilitate the identification of patients for inclusion on palliative care registers [10] and the prioritisation of patients who are referred to palliative care services.

The Prognosis in Palliative care Scales (PiPS) are predictive models of survival and were previously developed by members of our research team in order to provide an objective aid to clinicians’ intuition [9]. The original study recruited prospectively a cohort of 1018 patients with advanced cancer, who were no longer undergoing disease-modifying treatment. This was a multi-centre study involving 18 specialist palliative care services across England. Separate prognostic models were created for patients without (PiPS-A) or with (PiPS-B) available blood test results. The PiPS scores were able to predict whether a patient was likely to live for “days” (less than 14 days), “weeks” (between 2 and 7 weeks) or “months” (2 months or longer). These categories were chosen as they seemed to have the greatest face validity among clinicians. Both PiPS models were shown to perform as well as CES. The PiPS-B prognostic estimate was found to be significantly better than doctors’ prognostic estimates. Before recommending PiPS for use in routine clinical practice, it is important to check that the models provide accurate and reliable estimates of survival in a new group of patients.

More recently, two research studies have published validation data about the PiPS models [11, 12] in different clinical settings. Baba and colleagues (2015) [11] undertook an independent validation of the PiPS models in Japanese cancer patients and reported that the PiPS instrument performed as well as in Gwilliam’s original study [9]. However, the Japanese study did not compare the accuracy of PiPS to the accuracy of CES. Differences in cancer epidemiology and oncology practice between Japan and UK may also be a relevant consideration. The study by Kim and co-workers (2014) [12] reported that the PiPS instruments performed approximately as well as in the original study. However, the Kim study included a relatively small number of participants and the study population was restricted to palliative cancer patients in a specialist cancer hospital in South Korea. No large scale validation has yet been undertaken in the UK.

Taken together, these two studies strengthen the case for undertaking a large-scale validation study in the UK using CES as a comparator. Based on systematic reviews [13, 14], four other prognostic models have been identified that might also be useful in clinical practice and which are in need of further evaluation. These are the Palliative Prognostic Index (PPI) [15], the Palliative Performance Scale (PPS) [16], the Palliative Prognostic (PaP) [17] score and the Feliu Prognostic Nomogram (FPN) [18].

The PPI and the PPS can both be calculated without the need for a blood test (like PiPS-A). The PPI model stratifies patients into three groups; survival shorter than 3 weeks; shorter than 6 weeks; or more than 6 weeks [15]. The PPI has shown a high accuracy level in patients with short estimates of survival [19]. The PPS is a measure of functional status and is one of the variables included in the PPI score. Although not specifically designed as a prognostic instrument, and therefore lacking some face validity as a stand-alone prognostic tool, the PPS has been found to have prognostic significance in patients with advanced disease [20, 21]. Using data from large observational studies, the PPS can be used to predict the probability of dying across a range of survival times [20].

The PaP and the FPN, both require blood test results (like PiPS-B). The PaP score classifies patients into three risk groups based on a 30-day survival probability of less than 30%; between 30 and 70%; and more than 70% [17]. There is increasing evidence to support its validity in a variety of settings [22–26]. The total PaP score was shown in one study to be more accurate than a simple clinician prediction of survival [27]. One practical concern with the PaP score is that it relies on CES. This can make the PaP challenging to use when clinicians are unsure about survival times or when an “objective” estimate is required that is free from the influence of CES. The FPN predicts survival at 15, 30 and 60 days [18]. In one study the FPN was found to be more accurate than the PaP [18] and does not rely on subjective CES.

The PiPS2 study was designed with the overall aim of validating the accuracy of the PiPS-A and PiPS-B [9]. The primary objectives of the study are: to validate the PiPS models and; to compare the performance of PiPS-B against CES. The secondary objectives are to validate other selected prognostic models (PPI, PPS, PaP and FPN).

A nested qualitative sub-study has also been embedded in the PiPS2 study to assess the acceptability of the prognostic models to patients, carers and clinicians and to identify barriers and facilitators to clinical use. This is particularly relevant because in clinical practice it is often the relatives and carers of non-competent or semi-conscious patients who most wish to have access to accurate prognostic information.

## Methods

### Study design

This is a multi-centre, prospective, observational, cohort study to validate various prognostic models in patients with advanced, incurable cancer. The study involves patients from 28 palliative care services across England and UK and is sponsored by University College London.

Patients were recruited in three palliative care settings:community palliative care teams (including day hospice and palliative care outpatients)hospital palliative care teamsinpatient palliative care units

The planned recruitment period for the validation study was from August 2016 to the end in April 2018. At least three months after all recruitment has ended, a list of study participants will be sent to the Health and Social Care Information Centre (HSCIC) in order to determine dates of death. The accuracy of the studied prognostic models will then be compared against actual survival.

Following Medical Research Council Guidance [28] a subset of patients who agreed to participate in the main study, their next-of-kin (informal carers), patients who declined to participate in the main study, and health care professionals, were recruited into a nested qualitative sub-study to explore views about prognostication and the use of prognostic tools.

### Participants

The study involved both patients with or without capacity to consent to participate. Many patients at the end of their lives become confused, semi-conscious, and comatose or may have pre-existing cognitive impairment, they therefore frequently lack capacity to consent to participate in research. The inclusion of patients who lack capacity is therefore of great importance as the study population should be representative of those patients commonly seen in palliative care services. Capacity was assessed by the attending clinician using the Department of Health guidance [29]. If capacity was in doubt, the clinician carried out a capacity test as provided by the Royal College of General Practitioners’ Mental Capacity Act Toolkit for Adults in England and Wales 2011 [30].

#### Inclusion criteria

Patients with locally advanced or metastatic incurable cancer. A patient with incurable cancer has an estimated prognosis of survival of less than one year.Men and women aged 18 years or over.Patients who had recently been referred to palliative care services. Recent referral has various meanings across different palliative care settings. For a community, day hospice or palliative care outpatient, “recent” means that the patient should have had fewer than three previous contacts with the palliative care service before they are recruited to the study. For inpatient palliative care patients (including hospital support teams), “recent” referral means that the patient should have been first seen by a member of the palliative care team no more than 7-days previously. The date of referral was considered the date the patient had first been seen by a member of the relevant palliative care team.Sufficient English language skills for patients with capacity to read and understand the Patient Information Sheet and undertake study assessments.

#### Exclusion criterion

Patients receiving (or planned to receive) treatment with curative intent at the time of consent. Patients receiving palliative treatment were still eligible to participate.

### Study assessments

Data were collected at a single time point and were usually obtained from a review of the medical notes or from a discussion with clinical staff. If patients were able to respond to questions data might have partly been obtained directly from them. The data that were required for the calculation of each prognostic score are shown in Table 1.

**Table 1 Tab1:** Data required for the calculation of prognostic models

Variable	Prognostic model					
	PiPS-A	PiPS-B	PPI	PPS^a^	PaP	FPN
ECOG performance status	X	X				X
General health status	X	X				
Abbreviated Mental Test Score > 3	X	X				
Primary breast cancer	X					
Primary prostate cancer	X	X				
Distant metastases (any)	X	X				
Liver metastases	X					
Bone metastases	X	X				
Anorexia	X	X			X	
Dysphagia	X					
Dyspnoea	X		X		X	
Weight loss in last month	X					
Pulse rate	X	X				
Fatigue		X				
PPS^a^ score			X	X		
Oral intake			X			
Oedema			X			
Delirium			X			
CES					X	
KPS					X	
Time to terminal disease^b^						X
Blood Results:						
White blood count		X			X	
Lymphocyte count		X			X	X
Neutrophil count		X				
Platelet count		X				
Urea		X				
Albumin		X				X
Alkaline phosphatase		X				
Alanine transaminase		X				
C-Reactive protein		X				
Lactate dehydrogenase						X

^a^Despite PPS being designed as a measure of functional status, it does have prognostic significance and was therefore included in the prognostic models this study intends to validate. PPS is listed in both “Variable” and “Prognostic Model” sections as it is one of the variables used for the calculation of the PPI score ^b^Time to terminal disease refers to the time between the initial cancer diagnosis and the date at which the cancer became incurable (i.e., time at which deemed to be inoperable or became metastatic)

#### Demographic, disease and treatment related data and capacity recording

Demographic details of enrolled patients, such as age, gender and current patients’ location (e.g., home, hospital, hospice) were recorded. National Health Service (NHS) number and date of birth were also recorded to be sent to the HSCIC. Information on the nature and site of primary tumour and sites of metastases (if any) were also collected. Additionally, patients’ capacity to consent to participate in the study was documented.

#### Key symptoms

The presence or the absence of key symptoms was recorded (this was required for the scoring of the prognostic models); anorexia, dysphagia, dyspnoea, fatigue and weight loss.

#### Abbreviated mental health score

This is a test that assesses cognitive function [31]. This test is not applicable to patients without capacity, who were attributed scores of zero.

#### Clinical assessments

Clinical assessments included:Recording of the presence or the absence of ascites, peripheral oedema, delirium and decreased oral intake. Pulse rate was also measured over one minute.The Eastern Co-operative Oncology Group (ECOG) performance status [32]. This is a measurement of patients’ level of everyday functioning.A 7-point scale of observer-rated health status. The scores range from very poor (point 1) to excellent (point 7).The Karnofsky Performance Scale (KPS) [33] this is used to assess patients’ functional impairment.The PPS [16]. This is one of the prognostic models that this study aims to validate. It describes the patients’ current ambulatory level; activity level and extent of disease; self-care abilities; intake and conscious level.Estimation of the time to terminal disease by the clinicians. This is defined as the time elapsed between the diagnosis and development of incurable disease and is required to calculate the FPN.

#### Blood test results

For patients with capacity a fresh blood specimen must have been taken. For patients without capacity there was no requirement to take a fresh blood specimen, however if a blood sample was being taken for another reason as a part of routine clinical care within 72 h of study enrolment then the relevant tests were requested. Even if no new specimen was being taken from a patient without capacity, if relevant results were available within 72 h of being enrolled in the study then these results were recorded.

The blood test results required are: white blood count, lymphocyte count, neutrophil count, platelet count, urea, albumin, alkaline phosphatase, alanine transaminase, C-reactive protein, lactate dehydrogenase. Blood specimens were processed locally in the routine clinical laboratory using usual arrangements.

#### Clinicians’ estimates of survival

The attending doctor and nurse estimated survival of study participants independently. When the estimates agreed then this represented the combined multi-professional prediction. When they were discordant, the doctor and nurse discussed the case and reached a consensus. In order to characterise the prognosticators in more detail they were asked to provide information about themselves (i.e., age, gender, professional training and years of specialist experience). Clinicians were also asked to provide their prognostic estimates using a number of different formats in order to facilitate comparison with the outputs of the prognostic scores. Clinicians were asked: to provide approximate estimates of length of survival - “days” (0–13 days); “weeks” (2–7 weeks); “months+” (2 months or longer); to provide more specific estimates of survival to the nearest week (from < 1 week to > 12 weeks); to estimate the probability of survival at specific time points (1 day; 3 days; 7 days; 15 days; 30 days and 60 days).

### Data management

A study database for the storage, management and analyses of identifiable data has been developed via a secure web application named “REDCap” (Research Electronic Data Capture) and using the UCL Data Safe Haven secure system. This system has been certified to the ISO27001 information security standard and conforms to the NHS Information Governance Toolkit (http://www.ucl.ac.uk/isd/itforslms/services/handling-sens-data/tech-soln).

The rest of the (non-identifiable) study data have been sent to a separate database (i.e., electronic Case Report Form - eCRF) that has been created and supported by a company called “Sealed Envelope” (https://www.sealedenvelope.com/). Data from the paper CRFs have manually been transferred to the eCRFs by the researchers at each participating site.

A data monitoring plan has also been put in place to ensure optimal data quality across sites.

### Recruitment procedure

#### Patients’ identification

In each participating service, members of the clinical team maintained a screening log of all new referrals to the service. For the patients who were not eligible to participate, the screening log records the following information: age range, gender, reason for ineligibility.

#### Consent procedure

Study procedures differed between patients with and without capacity.

##### Patients with capacity

Eligible patients were approached by a member of the clinical team about participation in the study. If eligible patients were not approached by a team member then the reason for failure to do so was recorded on the screening log.

Potential participants who had been approached by a member of the clinical team were asked if they are be willing to speak to a member of the research team and are handed a Patient Information Sheet (PIS). A member of the research team then discussed the study with the patient and sought their consent to participate. For community patients this discussion might have occurred over the telephone. Written informed consent was usually obtained at least 24 h after the PIS had been handed out but could have been obtained on the same day if it was more convenient and acceptable for the patient to do so. If the patient declined to participate in the study then the reason for this (if known) was documented on the screening log.

##### Patients without capacity

For patients without capacity a personal consultee was sought for advice. For patients with no personal consultee, the advice of a nominated consultee was sought. The nominated consultee was usually another doctor working in the hospital/hospice (who was not involved in the research), a social worker, a chaplain or the patient’s General Practitioner (GP).

In a similar manner to the approach adopted for patients with capacity, consultees of patients without capacity were advised that it was usual practice to wait for 24 h before giving assent. If the consultee gave telephone advice for the patient to be included in the study but they are unable to visit the unit to provide written evidence of assent then verbal agreement was initially deemed to be sufficient to allow the research team to enrol the patient in the study and start data collection. However, in these circumstances an assent form was posted to the consultee to be signed and returned to the research team within two weeks of the patient being enrolled in the study. If no signed assent form was received then the patient was withdrawn from the study and all data were destroyed.

##### Patients with fluctuating capacity

Patients who temporarily lacked and then recovered capacity were informed about their involvement in the study and have the opportunity to withdraw or confirm participation [9].

### Outcome measures

#### Primary outcome measures

The survival of patients (measured from the date patients consented to participate), the CES and the predictions of the PiPS-A and the PiPS-B prognostic models.

#### Secondary outcome measures

The predictions produced by the PPI, PPS, PaP and FPN.

### Sample size

The sample size calculations are based on data collected during the original study [9].

#### For the comparison between PiPS-B model predictions and CES

PiPS-B is the primary model of interest for this research. To show at least a 5% improvement in correct predictions using PiPS-B compared to clinicians’ predictions, assuming 80% power and 5% significance level and using a McNemar’s test, a total of 1267 patients will be required. The formula and the software used for these calculations are based on the work produced by Machin and co-workers (2009) [34]. It is estimated that in order to obtain 1267 complete data sets it is be necessary to recruit 1334 patients with capacity (assuming 5% missing data). In order to recruit 1334 patients with capacity it is be necessary to recruit 1778 patients in total (assuming 25% of patients will lack capacity).

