#### For the validation of the PiPS models

To validate predictions from a risk model it has been recommended that the validation data should have at least 100 events [35]. The validation data for the proposed study will involve several centres. There is no guidance on sample size calculation for multi-centre validation data. We expect clustering of patients within centres to be minimal based on other studies in community care [36]. However, to be conservative we have inflated the number of events required in the validation data to 150. Assuming an event rate of 17.8%, based on the original study, we will require 843 patients to validate the PiPS-B model. In fact, 1778 patients will be recruited, most of who will be able to provide data for the validation of both PiPS-A and PiPS-B, thus this sample size will be more than adequate to validate both models. Using similar arguments, the proposed sample size will also be more than sufficient to simply validate the other prognostic models (i.e., PPI, PPS, PaP and FPN).

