##### Comparison between PiPS-B model predictions and CES

To compare the accuracy of the model predictions and CES, the primary analysis will focus on the PiPS-B model. McNemar’s test will be used to compare the proportion of overall patient deaths predicted correctly by PIPS-B with the corresponding proportion predicted correctly by clinicians.

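### The primary McNemar comparison is sized and tested as if patients were independent, so its 80% power and 5% error rate hold only if the paired difference hardly clusters by service

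*Protocol article*

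**What the plan says.** The sample-size section for the comparison of PiPS-B with clinicians' estimates of survival (CES) sets this aim: "To show at least a 5% improvement in correct predictions using PiPS-B compared to clinicians’ predictions". The test is McNemar's, with power of 80% at the 5% level, and the result of the calculation reads: "a total of 1267 patients will be required". Two inflations follow, for missing data ("it is be necessary to recruit 1334 patients with capacity (assuming 5% missing data") and for the 25% expected to lack capacity, which brings the total to 1778. There is none for clustering.

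Under Primary analyses, McNemar's test is to "compare the proportion of overall patient deaths predicted correctly by PIPS-B with the corresponding proportion predicted correctly by clinicians". No term for service or clinician is named.

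Clustering appears only in the next sample-size section, on validation of the PiPS models. There the article says: "We expect clustering of patients within centres to be minimal based on other studies in community care". It nevertheless adds a margin: "to be conservative we have inflated the number of events required in the validation data to 150". The starting point was 100 events.

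Under Study design: "The study involves patients from 28 palliative care services", in community, hospital and inpatient settings. Under Clinicians' estimates of survival, the attending doctor and nurse each make an estimate and settle disagreements by consensus.

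**The concern.** The same patients in the same services feed both analyses, but only the validation calculation carries a multi-centre margin. That calculation needs 843 patients and had slack within 1778. The McNemar calculation sets the recruitment target and has no margin.

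McNemar's test treats each patient's pair of results (PiPS-B right or wrong, CES right or wrong) as independent of every other patient's. PiPS-B is a fixed algorithm, whereas CES depends on local clinicians. If clinicians in some services predict better or more optimistically than in others, that variation enters the paired difference and makes patients within a service alike. The expectation of minimal clustering is drawn from community care, while two of the three settings are hospital teams and inpatient units, and it does not mention clinicians.

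At stake is the p-value behind the conclusion named in the Discussion, whether PiPS-B is significantly better than the multi-professional estimate. With positive clustering, an unadjusted test claims a difference too often.

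**Working it through.** **Inputs from the article.** Difference d = 0.05, power 80%, significance level 5% (taken as two-sided, since sidedness is not stated), n = 1267 complete pairs, 28 services, 5% missing data, 25% without capacity.

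**Inputs not in the article.** The discordant proportion ψ, which is back-solved below, and the ICC of the paired difference, which is assumed over a range. Services are taken as equal in size; unequal sizes would raise the design effect.

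**1. The plan's own figure.** The independent-pairs formula is

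n = [1.96·√ψ + 0.842·√(ψ − d²)]² / d².

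Setting n = 1267 gives ψ ≈ 0.404. So 1267 is a plausible McNemar figure with no design effect, though it cannot be reproduced from the stated inputs alone. The later steps agree: 1267/0.95 = 1334, and 1334/0.75 = 1778.7 (stated as 1778). For validation, 150/0.178 = 843.

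**2. Design effect.** Patients per service: m = 1267/28 = 45.25. DE = 1 + (m − 1)·ICC = 1 + 44.25·ICC.

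**3. Type I error if the ordinary McNemar test is kept.** 2·[1 − Φ(1.96/√DE)].

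**4. Power of a valid adjusted test.** Put n = 1267/DE into Φ{(d·√n − 1.96·√ψ)/√(ψ − d²)}, with √ψ = 0.636 and √(ψ − d²) = 0.634. For ICC 0.01: DE = 1.44, n = 878, and (0.05·√878 − 1.246)/0.634 ≈ 0.37, so power is about 64%.

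**5. Power of the unadjusted test against the 5% difference.** Φ{(d·√1267/√ψ − 1.96)/√DE}.

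| Assumed ICC | DE | Type I error, unadjusted | Power, unadjusted | Power, adjusted |
|---|---|---|---|---|
| 0 | 1.00 | 5.0% | 80% | 80% |
| 0.001 | 1.04 | 5.5% | 79% | 78% |
| 0.005 | 1.22 | 7.6% | 78% | 72% |
| 0.01 | 1.44 | 10.3% | 76% | 64% |
| 0.02 | 1.89 | 15.3% | 73% | 53% |

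The inflated error belongs to the unadjusted test and the larger power loss to the adjusted test. They are alternatives and do not occur together.

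**6. Possible margin.** The 1267 counts only patients with capacity. Under Blood test results, results within 72 h are also recorded for patients without capacity when available. As an upper bound, if 95% of all 1778 (1689) were usable, m = 60.3 and adjusted power would be about 81% at ICC 0.005 and 73% at 0.01. This does not repair the unadjusted test's type I error, which would be about 8.5% and 12.1%.

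**The case against.** The article expects centre clustering to be minimal and gives no ICC; at zero nothing is lost, and at 0.001 very little. The comparison is paired within patient, so service effects that move both predictions alike, such as case mix, cancel. Only clustering of the difference matters, and it may be near zero. The numbers of clinicians and of patients per clinician are not given, so a clinician effect is a reasonable inference that cannot be sized. The article is condensed, and an analysis plan that is not shown may name an adjusted test. All of this stands, and it makes the loss conditional.

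Two stronger readings are tempting. A reader might infer that the trial fails to deliver 80% power and 5% error. The article does not support that, because it contains no figure for the clustering.

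A reader might also carry the validation margin (150/100 = 1.5) to the primary test and conclude that its power is 63%. That margin raises a rule-of-thumb event count for a different purpose and is not a design effect for a paired test. It would not even transfer as 1.5: at 843/28 = 30.1 patients per service it implies an ICC of 0.5/29.1 = 0.017, which at 45.25 per service gives a design effect of about 1.76. The 63% would also apply only to an adjusted test; the planned test at a design effect of 1.5 keeps about 75% power, with about 11% type I error.

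What the objection does not remove is that the calculation and the test, as written, rest on an independence assumption that is neither stated nor justified for the primary comparison.

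**Conclusion.** The point holds as a conditional one. The primary calculation and test assume independent pairs, while the multi-centre allowance was made only where there was already slack. The nominal 80% power and 5% error are right only if the ICC of the within-patient difference in correctness is close to zero. Over an assumed range of 0.001 to 0.02, type I error of the unadjusted test runs from about 5.5% to 15.3%, and power of an adjusted test on 1267 pairs from about 78% to 53%. These figures rest on a two-sided test, a back-solved discordance of 0.404, 28 equal services and only the 1267 planned pairs. The sample-size inconsistency is the firmer part, since the unseen analysis plan may settle the test.

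**What to change.** **Analysis section on PiPS-B against CES.** Compare the paired proportions correct with a McNemar test for clustered data, or with a service-level cluster-robust standard error for the paired difference, referred to t with the number of services minus 1 degrees of freedom (27 for 28 services). Clustering on service also covers clinicians who work within one service.

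**Sample-size section for the same comparison.** State that 80% power assumes no clustering of the paired difference. Give the range above as a sensitivity, with the ICCs labelled as assumptions, and do not present 63% as the trial's power.

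**Cost.** Wording and a few lines of code, with no new data and no extra patients. Recruitment has closed, but the article places death linkage and the accuracy comparison after it, so the test can be fixed before results are known. The price is a less favourable stated power and somewhat wider intervals. If clustering is nil, the t reference alone widens them by about 5% (2.052/1.960 = 1.047), and the result should otherwise barely change.
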